#### Recruitment

Recruitment will begin at the cluster level. Potential participants – dyads for whom driving cessation is a current issue (including those still planning, those who have stopped and those who should have stopped) – will be recruited on a rolling basis across 2.5 years via primary and secondary care clinics, community agencies, service providers, local media, social media, dementia support groups, and word of mouth. Participants will be invited to contact the researchers to obtain further details of the study, or to give their verbal permission to their health professional (e.g. general practitioner, neuropsychologist,) to pass on their contact details for the researchers to follow up, for the purpose of providing more information about the study.

#### Outcomes and assessment tools

##### Main outcome measure

The main outcome measure for persons with dementia and their family members is lifespace – the geographic space in which a person lives and conducts their activities. It is recognized that having dementia is likely to constrict a person’s lifespace and reduce their community participation. Lifespace will be captured through two measures, (i) the number of episodes away from home (during the past week); and (ii) novel Smartphone GPS technology used to passively measure lifespace metrics for people with dementia and their care partners. Participants will carry a study smartphone in a comfortable case (provided to them by the researcher – on loan and at no cost) for the period of one week pre- and one week post-intervention and one-week at three-month follow-up. Support is provided to make sure the purpose of the phone is understood and remembered by participants. Data stream to a secure portal and can enable the research team to identify if a problem with data collection has occurred. Family members are asked to remind the person with dementia to wear the smartphone. While the limitations of this method are acknowledged, strategies will be in place to mitigate these. This type of data collection approach has been used successfully with this population. An ‘episode away from home’ is defined by a single occurrence of leaving the home, counted for the previous week, which is collected by Smartphone and App from persons with dementia, and by self-report from them and/or their care partners.

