## Background

Stopping driving impacts the health and quality of life of people with dementia and their care partners. It also poses considerable challenges to health professionals who monitor driving issues and to those involved in testing and licensing. Without intensive practical and emotional support to plan for, and eventually, cease driving, people with dementia are at high risk for increased depression, anxiety, grief, social isolation, unsafe and unlicensed driving and injury. We have developed a comprehensive support- and education-based intervention targeted at people with dementia and their care partners and family members to manage driving cessation. The intervention is a translation of a proven driving cessation intervention for people without cognitive decline and has been trialled in an intensive case study. This project investigates the effectiveness of the evidence-based driving cessation intervention for people with dementia and their family members who are retiring from driving, through a cluster randomized controlled trial.

A diagnosis of dementia does not mean the immediate cessation of driving [1, 2]. However, at some stage people with dementia will need to stop [3]. Without necessary support programs in place, many people living with dementia avoid the issue until it is reaches a crisis point [4]. Health professionals acknowledge the complexity of driving and driving cessation issues for people with dementia, and studies identify that their lack of knowledge and confidence in managing driving cessation issues may lead to reluctance to do so [5]. Some drivers with dementia avoid their responsibility to stop driving even when their licence is terminated for emotional, logistical, and mobility reasons, or due to a lack of insight and awareness of the dangers [2, 4, 6]. Driving cessation can diminish ‘lifespace’ – defined as the extent of movement through the environment that captures lived community mobility [7] – constricted lifespace may lead to more rapid cognitive decline [8–10].

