### Aims and objectives

The primary aim of this study is to assess the impact of participating in the CarFreeMe intervention on lifespace compared to usual care, for people with dementia. The secondary aim is to assess the impact of CarFreeMe on quality of life, wellbeing, and self-efficacy for people with dementia and their care partners, compared to usual care.

The objectives are to:Maintain or increase community mobility outcomes for people with dementia who are transitioning to driving cessation (or have recently ceased driving);Increase use of safe alternative modes of transport;Evaluate the impact of the intervention on self-efficacy, wellbeing, and community participation of people with dementia;Evaluate the impact of the intervention on self-efficacy, wellbeing, and community participation of the care partners/family members of people with dementia.

It is predicted that compared with usual care, the driving cessation intervention:Maintains or increases *lifespace* – as measured by metrics collected via a custom Smartphone app;Maintains or increases *episodes away from home* and using safe modes of transport – as measured by metrics collected via Smartphone and App, and self-report;Results in participants:greater self-efficacy in dealing with driving cessation decision making;higher measures of wellbeing;decreased measures of depression, anxiety, isolation, and stress.

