##### Secondary outcome measures

‘Safe transport status’ is the major secondary outcome measure. We will collect information from participants about the mode of transport used for each episode away from home (e.g. walk, taxi, bus), counted for the previous week, and about any concerns they had about the mode of transport used (e.g. safety). Other secondary outcome measures include wellbeing, depression, anxiety, self-efficacy and self-performance and isolation, which will be collected from dyads; as well as caregiving strain collected from carer/family member only (see Table 2). At baseline, general questions related to demographics, mobility, proximity to services, usual transport used, community involvement, socioeconomic status, and the circumstances surrounding driving cessation (e.g. participant is the only driver in household, participant’s readiness to transition to retired driver), will be collected.

**Table 2 Tab2:** Pre- and post-intervention measurement tools relating to persons with dementia and family members/care partners, collected at Times 1, 2, and 3

Person with dementia	Family Member	Measure
Lifespace; Episodes away from home	Lifespace; Episodes away from home	Lifespace metrics via Smartphone GPS data; Self-report, Life Space Questionnaire [19]
Mode/s of transport used in previous week	Mode/s of transport used in previous week	Semi-structured Interview
Readiness for transitioning to non-driver		Assessment of Readiness for Mobility Transition [20]
Social Isolation	Social Isolation	Loneliness Scale [21]
Wellbeing/Quality of life	Wellbeing/Quality of life	Personal Wellbeing Index [22]
	Caregiver Strain	Caregiver Burden Index [23]
Self-efficacy - Transport and lifestyle	Caregivers Self-efficacy	Transport and Lifestyle Self Efficacy [13]
Depression and Anxiety symptoms	Depression and Anxiety symptoms	Geriatric Depression Scale [24]; Geriatric Anxiety Inventory [25]
Individualized goal setting (and achievement of goals)	(completed together)	Canadian Occupational Performance Measure [26]
Perceptions of needs and experiences, feedback	Perceptions of needs and experiences, feedback	Semi-structured interviews with sub-sample

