### Data analysis

Baseline demographic and cluster characteristics will be compared between the intervention and control groups. Data will be analysed using random effects models with maximum likelihood estimation. All analyses will be conducted at the individual and aggregated cluster levels using generalized estimating equations to adjust for clustering effects within geographical location, and adjusting for intracluster correlations between individuals, and according to intention to treat principles.

Hypotheses 1 & 2. Increase in lifespace and the rate of episodes away from home will be analysed at the cluster level using a linear mixed effects model with random intercepts used to analyse the effect of the intervention on number of episodes away from home.

Hypotheses 3 & 4. Testing the effect of the intervention on self-efficacy, wellbeing, depression symptoms, anxiety symptoms, and social isolation, will involve linear mixed effects model.

Qualitative analyses will include thematic analysis of the semi-structured interviews with participants. Coding will be conducted and verified by minimum three members of the research team. The group will convene to review themes until consensus is reached.

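### Hypothesis 2 joins episodes away from home with safe transport, but its stated analysis uses only lifespace and an all-mode count, which cannot separate self-driven trips given up from a failure to gain alternatives

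*Protocol article*

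**What the plan says.** - **Aim (Protocol article, Aims and objectives).** The article puts it this way: "The primary aim of this study is to assess the impact of participating in the CarFreeMe intervention on lifespace compared to usual care". The first prediction concerns lifespace. The second joins episodes away from home with the use of safe transport.
- **Outcome (Main outcome measure).** Lifespace is captured by smartphone GPS metrics and by weekly episodes away from home. An episode "is defined by a single occurrence of leaving the home, counted for the previous week". The definition sets no condition on the means of transport or on who is at the wheel.
- **Sample (Recruitment).** Dyads for whom driving cessation is a live issue are eligible, including "those still planning, those who have stopped and those who should have stopped".
- **Mechanism (Background).** "Driving cessation can diminish" lifespace, in the article's own account.
- **Mode (Secondary outcome measures).** Safe transport status ranks as the major secondary outcome. It draws on "the mode of transport used for each episode away from home", with walking, taxi and bus as examples. Table 2 places mode of transport at Times 1, 2 and 3.
- **Analysis (Data analysis).** Hypotheses 1 and 2 are tested through lifespace and the rate of episodes, in a linear mixed model with random intercepts. Hypotheses 3 and 4 name self-efficacy, wellbeing, depression, anxiety and social isolation. Safe transport status appears under neither. On baseline data the section says: "Baseline demographic and cluster characteristics will be compared between the intervention and control groups".

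**The concern.** The programme supports people who are giving up driving. If it leads more people in the intervention arm to stop, that arm loses self-driven trips while controls who go on driving keep theirs. Trips gained by bus, taxi, walking or lifts push the count the other way. An all-mode count reports only the net of the two.

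Two consequences follow for hypothesis 2. A null result could mean that no alternatives were gained, or that they were gained and offset by driving given up; these are different findings for anyone deciding whether to adopt the programme. Conversely, a positive result could come partly from trips driven by people whom the protocol itself describes as needing to have stopped, although the prediction speaks of safe transport.

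**Working it through.** **The passages side by side**

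| Element | Hypothesis 2 as predicted | Hypothesis 2 as analysed |
|---|---|---|
| Leaving home | Episodes maintained or increased | Count of all episodes |
| Means of transport | Safe modes used | Not used |
| Self-driven trip by someone who should have stopped | Hard to reconcile with safe use | Adds 1, like a bus trip |

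Mode is recorded for each episode, so the information needed for the middle row is largely collected already.

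**What the net count hides**

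The plan gives no figure for this, so there is none to reproduce. The Sample size section supplies only the target difference, 1 episode per week. Assumed quantities, none of them in the article:
- g = mean gain per person in weekly episodes by other modes, intervention minus control;
- q = extra share of the intervention arm that stops driving;
- L = weekly self-driven episodes that each of these people gives up;
- people who go on driving drive as before.

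Then: self-driven effect = −qL; other-mode effect = g; all-mode effect = g − qL.

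The offset qL runs from 0.10 × 1 = 0.1 to 0.30 × 3 = 0.9 for q of 10 to 30 percentage points and L of 1 to 3. With g = 1, equal to the target:

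| q | L = 2 | L = 3 | L = 5 |
|---|---|---|---|
| 0.1 | 0.8 | 0.7 | 0.5 |
| 0.2 | 0.6 | 0.4 | 0.0 |
| 0.3 | 0.4 | 0.1 | −0.5 |

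Three different situations give the same all-mode result of +0.4 (the third drops the assumption about continuing drivers):

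| Situation | Self-driven | Other modes | All modes |
|---|---|---|---|
| Many stop (q = 0.3, L = 2), alternatives gained | −0.6 | +1.0 | +0.4 |
| Nobody extra stops, small gain in alternatives | 0 | +0.4 | +0.4 |
| Intervention arm simply drives more | +0.4 | 0 | +0.4 |

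Only the split by mode tells them apart.

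**What baseline covariates can do**

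Stopping because of the programme happens after randomisation, so adjusting for Time 1 values leaves −qL in the contrast. Their use is precision and chance imbalance.

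- Precision: residual variance falls by a factor 1 − r². For an assumed correlation r of 0.3, 0.5 or 0.7 the reduction is 9%, 25% or 49%.
- Imbalance: SE of the baseline difference between arms = √(2 × SD² × DEFF / (k × m)), with SD = 3.16 (SD² = 9.986), ICC = 0.05, DEFF = 1 + (m − 1) × 0.05 and k = 5 clusters per arm (the stated minimum of 10, read as a total).
  - m = 15: DEFF = 1.70; SE = √(33.95 / 75) = 0.673.
  - m = 12 (after 20% dropout): DEFF = 1.55; SE = √(30.96 / 60) = 0.718.
  - Probability of a chance difference above 1, the target: z = 1.49 and 1.39, so about 14% and 16%. Above 0.5, half the target: 46% and 49%.

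These SEs ignore the matching of clusters, which may reduce them. The section also says that more than the minimum number of clusters will be included.

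**The case against.** **Mobility is the declared construct.** The primary aim is lifespace, which the Background treats as community mobility as it is lived. If someone stops driving and goes out less, that is a real loss on this construct. A reader might infer that the primary outcome scores success as failure. The documents do not support this: stopping driving is not the primary endpoint, and transport safety is given to the major secondary outcome. This stands, and it is why the all-mode count should remain. It does not answer the narrower point that hypothesis 2 itself includes safe transport and its stated analysis does not.

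**Silence on covariates.** A reader might also infer that the primary model omits baseline episodes and baseline driving status. The article lists no fixed effects at all, and an analysis plan that is not shown may supply them. The text speaks of an increase, and outcomes are measured at three times, so a change analysis or a repeated-measures model would already use Time 1 episodes. No error can be claimed here. The absence of a named analysis for safe transport status is likewise partly silence; the point rests on the mismatch between the second prediction and the analysis stated for it.

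**Adjustment as a cure.** It may seem that a driving-status covariate would resolve the ambiguity. It would not, as the working shows. Nor is a baseline imbalance as large as the target effect the likely outcome: its probability is about one in seven with 10 clusters, and lower with more.

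**Moving the claim to trips not driven by the participant.** This errs the other way. Someone who replaces five driven trips with two taxi rides gains 2 on that count while going out three times less. The split should accompany the all-mode count, not replace it.

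**Data.** The examples of mode do not mention driving, and nothing says that a car trip is recorded as driver or passenger. The split may therefore need one additional code.

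**Conclusion.** The point holds in a limited form. The stated analysis of hypothesis 2 covers only part of the prediction. In a sample of current and former drivers, the all-mode count cannot by itself distinguish driving given up from alternatives not gained, and it credits self-driven trips by people who should have stopped. This is a fault of interpretation and of fit between hypothesis and analysis; it does not invalidate the primary lifespace measure.

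The size of any masking cannot be derived from the article. The 0.1 to 0.9 episodes shown against a target of 1 rest wholly on assumed values of q and L. They show that the offset could matter, not that it will. The change is worth making before outcome data are seen, because the same split chosen afterwards would look data-driven.

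**What to change.** 1. Keep the all-mode count as a primary lifespace measure.
2. For hypothesis 2, prespecify a companion analysis for the person with dementia: weekly episodes split into self-driven and other modes, compared by arm in the same mixed model at Times 2 and 3, using the mode recorded for each episode.
3. Make sure that the transport interview codes each car trip as driver or passenger.
4. State that the primary result will be interpreted jointly with this split, and name the analysis of safe transport status.
5. Include Time 1 episodes and Time 1 driving status (still driving or stopped) as covariates, described as serving precision and chance imbalance only. Confirm that the baseline questions on driving circumstances yield this status.

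Possible wording: *Hypothesis 2 will be assessed by the all-mode count together with self-driven and other-mode episodes, each compared between arms in the same mixed model; the three results will be presented and interpreted together.*

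Cost: one coding distinction, one extra table and a few degrees of freedom. No new visit or instrument is needed.

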##### Secondary outcome measures

‘Safe transport status’ is the major secondary outcome measure. We will collect information from participants about the mode of transport used for each episode away from home (e.g. walk, taxi, bus), counted for the previous week, and about any concerns they had about the mode of transport used (e.g. safety). Other secondary outcome measures include wellbeing, depression, anxiety, self-efficacy and self-performance and isolation, which will be collected from dyads; as well as caregiving strain collected from carer/family member only (see Table 2). At baseline, general questions related to demographics, mobility, proximity to services, usual transport used, community involvement, socioeconomic status, and the circumstances surrounding driving cessation (e.g. participant is the only driver in household, participant’s readiness to transition to retired driver), will be collected.

**Table 2 Tab2:** Pre- and post-intervention measurement tools relating to persons with dementia and family members/care partners, collected at Times 1, 2, and 3

Person with dementia	Family Member	Measure
Lifespace; Episodes away from home	Lifespace; Episodes away from home	Lifespace metrics via Smartphone GPS data; Self-report, Life Space Questionnaire [19]
Mode/s of transport used in previous week	Mode/s of transport used in previous week	Semi-structured Interview
Readiness for transitioning to non-driver		Assessment of Readiness for Mobility Transition [20]
Social Isolation	Social Isolation	Loneliness Scale [21]
Wellbeing/Quality of life	Wellbeing/Quality of life	Personal Wellbeing Index [22]
	Caregiver Strain	Caregiver Burden Index [23]
Self-efficacy - Transport and lifestyle	Caregivers Self-efficacy	Transport and Lifestyle Self Efficacy [13]
Depression and Anxiety symptoms	Depression and Anxiety symptoms	Geriatric Depression Scale [24]; Geriatric Anxiety Inventory [25]
Individualized goal setting (and achievement of goals)	(completed together)	Canadian Occupational Performance Measure [26]
Perceptions of needs and experiences, feedback	Perceptions of needs and experiences, feedback	Semi-structured interviews with sub-sample

##### Interviews

In addition, we aim to interview a sub-sample of participants – participants in the intervention condition – at (i) pre- and (ii) post-intervention to ascertain an understanding of their experiences, decision-making, timing of driving decisions and events that influenced these decisions, and about their experiences of the intervention (e.g. what worked well, didn’t work well, what made a difference, whether their needs were met, and what issues they experienced going through the process). These interviews will be conducted by a researcher by telephone or in-person and will therefore be separate from blinded assessments at Times 2, and 3. The interviews will be approximately 15–30 min duration. These will be audio recorded and transcribed verbatim and later thematically analysed. Those that consent to being followed up by telephone or email will be given an opportunity to member check the researchers’ findings in relation to themes that emerge from the transcribed data. These participants will therefore be contacted again, after all data are collected and analysed.

##### Determining severity of cognitive decline

The CDR scale will be used to determine participants’ severity of dementia, for the purposes of sample description. A global CDR of 0 indicates no dementia. A CDR of 0.5 represents very mild dementia or in some cases with minimal impairment, uncertain or questionable dementia. A CDR of 1, 2, or 3 corresponds to mild, moderate, or severe dementia, respectively. Participants’ score on the CDR [17] screening tool will be used to aggregately describe the sample in any written reports or manuscripts (e.g. X participants with mild dementia, X with moderate dementia, according to the CDR).

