### Participants

#### Eligibility criteria

*Persons with dementia* will be older people (aged 65 years and over), male or female, with mild cognitive impairment or mild or moderate dementia of any type, and driving or driving cessation is a current issue for them. Persons living with dementia will be able to provide informed consent to participate or (where determined necessary) to have a care partner that can provide proxy informed consent on their behalf. People with a diagnosis of younger-onset of dementia are excluded from this study because the program has not been translated for people with younger-onset dementia as yet. Non-English speaking participants will be excluded from participating because the intervention at present does not cater to a non-English speaking audience. Potential participants with dementia will be screened using the Clinical Dementia Rating scale (CDR) [22]. Participants with scores of 2 or less will be eligible to participate (0.5 = very mild dementia, 1 = mild dementia, 2 = moderate dementia).

*Care partners/support persons* self-identified informal primary care partners of the retired/retiring driver with dementia are eligible to participate alongside that person. To be eligible support persons may be male or female, and must be aged 18 years and over, have the ability to communicate in English, and be providing ongoing support to the person with the dementia.

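### Screening dementia severity (CDR) is given only a descriptive use; naming it as a prespecified covariate would give modest precision and protect against recruitment-driven imbalance at almost no cost

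*Protocol article*

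**What the plan says.** The article gives the CDR two roles. Under Eligibility criteria it is a screening tool: "Participants with scores of 2 or less will be eligible to participate". Under Determining severity of cognitive decline it serves to determine "severity of dementia, for the purposes of sample description", and the same section adds that the "screening tool will be used to aggregately describe the sample in any written reports or manuscripts".

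The Data analysis section plans random effects models by maximum likelihood, together with analyses "using generalized estimating equations to adjust for clustering effects within geographical location, and adjusting for intracluster correlations between individuals". For the primary outcome it names a "linear mixed effects model with random intercepts used to analyse the effect of the intervention on number of episodes away from home". It also says that "Baseline demographic and cluster characteristics will be compared between the intervention and control groups". It lists no baseline covariate and rules none out.

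On severity as a predictor, the Main outcome measure section says: "It is recognized that having dementia is likely to constrict" a person's lifespace and lower their participation. Eligibility runs from mild cognitive impairment to moderate dementia.

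Design and Randomisation and blinding match regions on demographics, population density, and transport and health infrastructure. Severity is not on the list. Regions are randomised before baseline measurement, and Recruitment describes rolling entry over 2.5 years.

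**The concern.** The plan already holds a baseline variable that it has reason to think predicts the primary outcome, and it assigns that variable to description. Nothing else in the stated design controls severity: it is not a matching factor, it is not a named covariate, and individuals are not randomised.

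Two things are at stake. The first is precision: the part of the outcome variance that severity explains stays in the error term. The second is recruitment after allocation. People come in through clinics, media and word of mouth once their region's arm is fixed. A researcher takes the first call and screens, and the blinding described is that of the outcome assessors. If the severity mix of those enrolled differs by arm for that reason, the difference is systematic, and an analysis without severity does not correct for it.

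A smaller issue is dropout, planned at 20%. A likelihood analysis without CDR has to assume that dropout is unrelated to severity once the recorded outcomes are taken into account.

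**Working it through.** **Inputs from the article (Sample size).** Target difference 1 episode per week; SD 3.16, so variance 9.986; ICC 0.05; 15 dyads per region on average; 20% dropout; at least 10 regions. The illustration takes 5 regions per arm with 15 × 0.8 = 12 analysed in each. That is 60 per arm, with design effect 1 + 11 × 0.05 = 1.55. The article has no figure on severity to reproduce. Whether 10 regions are enough is a separate question; 10 is only the setting here.

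**Assumed inputs, none of them in the article.** 30% of participants at CDR 2; an ICC of 0.05 for severity; CDR 2 participants make d = 1, 2 or 3 fewer trips per week.

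**Step 1: size of a chance imbalance.** SD of the between-arm difference in the CDR 2 share = √(2 × 0.3 × 0.7 × 1.55 / 60) = 0.104. A gap of 10 points or more has probability 0.34, and the 95% limit is 1.96 × 0.104 = 0.204. With no dropout (75 per arm, design effect 1.70) the SD is 0.098 and the probability 0.31. With 10 regions per arm and 12 analysed in each, the SD is 0.104/√2 = 0.074.

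**Step 2: what it does to an estimate with neither CDR nor baseline outcome in the model.** A 1-SD imbalance shifts it by 0.104 × d = 0.10, 0.21 or 0.31 episodes.

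**Step 3: where that shift sits.** The unadjusted standard error is √(2 × 9.986 × 1.55 / 60) = 0.718, a variance of 0.516. At d = 3 the chance shift has variance 9 × 0.104² = 0.098. Taking it out leaves 0.418, a standard error of 0.647. The shift is therefore not an extra error on top of the standard error; it is already inside it. The gain from adjustment follows from the share of variance explained, 0.21 × d² / 9.986:

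| d | variance explained | adjusted SE | cut in SE |
|---|---|---|---|
| 1 | 2.1% | 0.711 | 1.1% |
| 2 | 8.4% | 0.687 | 4.3% |
| 3 | 18.9% | 0.647 | 9.9% |

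The proportional cut does not depend on the number of regions.

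**Step 4: with the Time 1 outcome in the model.** Episodes and lifespace are measured at Times 1, 2 and 3.
- In an analysis of change, a constant severity effect cancels. What remains is severity's effect on change up to about week 20, for which the article gives no figure.
- With Time 1 as a covariate, an assumed correlation of 0.5 between Time 1 and follow-up and the same severity effect at both, half the shift remains: 0.05 to 0.16 for a 1-SD imbalance. With r² the variance explained in Step 3, the further share that CDR explains is 0.25 r² / [0.75 (1 − r²)] = 0.7%, 3.1% and 7.8%. The cut in standard error falls to 0.4%, 1.5% and 4.0%.

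**Step 5: recruitment-driven imbalance.** This part is not in the standard error. Without the baseline outcome, each 10-point systematic difference in the CDR 2 share would move the estimate by 0.10 × d = 0.1 to 0.3 episodes, against a target of 1. The article gives no basis for saying how large such a difference would be.

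**The case against.** The strongest reply is that this argues from silence. The article is condensed, no statistical analysis plan is shown, and a covariate list usually belongs there. That stands against a reader who might infer that the primary analysis ignores or excludes CDR: the documents do not say so. It does not dispose of the point, because the article does more than stay silent. It states a purpose for the severity score, and that purpose is description.

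A reader might also infer that severity is the trial's main prognostic factor. The documents do not support that. They say dementia is likely to narrow lifespace; they do not rank CDR grades within this sample. The Background also says that stopping driving can diminish lifespace, and Recruitment takes people still planning, people who have stopped and people who should have. Expected prognostic factor is as far as the text goes.

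A third tempting reading is that any severity imbalance passes straight into the effect estimate. It does not. The outcome is measured at Time 1, and a model that uses it removes some or all of a constant severity effect. Chance imbalance is also variance already counted in the standard error, and pair-matching may reduce it further. Both objections stand, and they reduce the size of the point.

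Finally, no passage links dropout to severity. Adding CDR helps only for dropout that depends on screening CDR and recorded outcomes. It does not cover dropout driven by later decline that was not observed.

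**Conclusion.** The point holds in a limited form. Beyond screening, CDR severity has only a descriptive purpose in the article, the models name adjustment for clustering only, and regions are not matched on severity. Severity is an expected prognostic factor and participants enter after allocation, so an imbalance between a small number of regions can enter the estimate, mainly through severity's effect on change if the Time 1 outcome is modelled.

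The gain is modest: a cut of roughly 1% to 10% in the standard error without the baseline outcome, and about 0.4% to 4% with it at an assumed correlation of 0.5. All of this rests on assumed inputs (30% at CDR 2, severity ICC 0.05, 1 to 3 fewer trips per week). Protection against recruitment-driven imbalance is the further benefit, and it cannot be quantified from the documents. This is a worthwhile and nearly free improvement; it does not show that the planned comparison is invalid.

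**What to change.** In Determining severity of cognitive decline, add that screening CDR will also be a prespecified covariate in the analysis. In Data analysis, state that the primary and secondary models for persons with dementia include, whatever balance is observed:
- screening CDR as an individual-level fixed effect, with categories covering every eligible score (the rule of 2 or less does not literally exclude 0);
- the Time 1 value of the outcome.

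The primary analysis is described as being at the cluster level. If a cluster-level analysis is used, say that CDR enters through a first-stage individual-level adjustment before the regions are compared.

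Describe the effect on missing data with care: missing at random becomes more plausible for dropout that depends on screening CDR, and no more than that.

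Cost: a few sentences in the protocol or analysis plan, no new data, and a few individual-level degrees of freedom. Fixing the covariates now also avoids a choice made after an imbalance has been seen.
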